##### Fear of falling

Fear of falling is a significant predictor of future falls and can be assessed using the Falls Efficacy Scale (FES). The FES assesses patients’ perception of balance and stability during usual activities of daily living [57, 58]. The test-retest reliability is adequate within the geriatric population (*r* = 0.71) and the instrument has excellent internal consistency (Cronbach’s alpha = 0.91) [57]. Furthermore, scores on the FES have been shown to be moderately to highly correlated with other measures of balance confidence (*r* = 0.55–0.86) [59].

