#### Adverse events

We will measure the presence of adverse events that may be associated with each of the interventions. This will take place following each visit for participants enrolled in Group 1. For participants enrolled in Group 1 and 2, adverse events will be assessed at each follow-up visit. We will define adverse events as an unintended sign or symptom of the intervention. These include: significant increase in back and/or lower extremity pain, numbness, tingling, tiredness or claudication and cauda equine syndrome. We will compute the incidence (95 % CI) of each adverse event listed above. The cumulative number of visits will be used as the denominator. Any adverse event that is life threatening or associated with significant disability will be reported to the Mount Sinai Hospital Ethics Review Board.

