There is a high risk of falls in the LSS population and we need to ensure safety of participants while performing the SPWT. We will train assessors accompanying participants during the SPWT and practice procedures to reduce the risk of falls during the SPWT.

Participants randomized to the single instructional session may not follow the provided instructions, or may perform the exercises incorrectly leading to potential for injury. We will incorporate a safety monitoring protocol and provide participants the opportunity to contact us in an effort to reduce the risk of harm to participants randomized to this intervention.

LSS is a chronic arthritic condition whose prevalence, personal and economic burden is growing exponentially due to the aging population. The vast majority of individuals with LSS receive non-surgical care however, what constitutes effective non-surgical care is unknown. A multi-modal approach with a focus on self-management strategies as outlined in this proposal may be a practical and effective means to improve walking ability, functional status and quality of life in this population.

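### The stated adverse-event analysis would not report falls or injuries, although the protocol calls falls a high risk in this population

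*Protocol article*

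**What the plan says.** The *Adverse events* section of the protocol article fixes three things.

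- **Definition:** "We will define adverse events as an unintended sign or symptom of the intervention".
- **List:** "These include: significant increase in back and/or lower extremity pain, numbness, tingling, tiredness or claudication and cauda equine syndrome".
- **Analysis:** "We will compute the incidence (95 % CI) of each adverse event listed above". On the denominator it adds: "The cumulative number of visits will be used as the denominator".

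On ascertainment, Group 1 is asked after every visit, and "For participants enrolled in Group 1 and 2, adverse events will be assessed at each follow-up visit". Life-threatening or seriously disabling adverse events go to the ethics board.

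Falls appear elsewhere. The Discussion states "There is a high risk of falls in the LSS population" in connection with the self-paced walking test (SPWT), and answers it with assessor training and practised procedures. The same part of the Discussion says that Group 2 participants may do the exercises incorrectly and be injured. It mentions a safety monitoring protocol, whose content is not given, and an opportunity to contact the study team. The *Fear of falling* section justifies the Falls Efficacy Scale (FES) on the ground that "Fear of falling is a significant predictor of future falls".

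**The concern.** The hazard that the Discussion singles out does not reach the section that says what will be counted. A fall is an event, not a sign or symptom. A fall during the SPWT arises from an assessment, and a fall in daily life is not clearly caused by either intervention. Under the definition and list as written, neither has a defined place in the safety results. The same holds for an exercise injury that does not show itself as one of the listed symptoms. Reporting to the ethics board applies to adverse events, so it inherits the same definition.

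This matters because both arms receive a home exercise programme in a trial meant to increase walking, with very different supervision: twelve sessions and a booster in Group 1, one session in Group 2. Falls could become more or less frequent with the programme. A report that followed the stated analysis exactly would not show which.

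**Working it through.** **1. Passages side by side**

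| Question | Where | Answer in the protocol article |
|---|---|---|
| Are falls recognised as a risk? | Discussion | Yes, high in this population; raised for the SPWT |
| Is injury recognised as a risk? | Discussion | Yes, in Group 2 from incorrectly performed exercises |
| Are falls or injuries in the adverse-event list? | Adverse events | No |
| Does the definition reach them? | Adverse events | Only as a sign or symptom of the intervention |
| Which events get an incidence? | Adverse events | Those listed |
| Does another stated measure count falls? | Table 2; Fear of falling | No; the FES is perception of balance and stability |
| What is done about falls in the SPWT? | Discussion | Prevention; no recording is stated |

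**2. Unequal contact**

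Scheduled occasions at which adverse events are asked about:

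- Group 1: 12 treatment sessions + 1 booster + 4 follow-ups = 17 (taking the booster as a visit).
- Group 2: 4 follow-ups.

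Unprompted mention of a fall therefore has about four times as many openings in Group 1 (17/4 = 4.25).

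The visit denominator would also distort falls if they were simply added to the list. Take 20 % fallers in each arm (assumption), one fall each: 0.20 × 52 = 10.4 events per arm. If the denominator is formed by arm:

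- Group 1: 10.4 / (52 × 17) = 0.0118 per visit.
- Group 2: 10.4 / (52 × 4) = 0.050 per visit.

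Equal fall risk would look like a fourfold difference. Falls should therefore be counted per participant.

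**3. The number per arm**

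The *Sample size* section gives 52 per group (30 % v 60 %, two-sided alpha 0.05, power 0.8, 20 % drop-out). With the pooled-variance formula:

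n = [1.96 √(2 × 0.45 × 0.55) + 0.8416 √(0.3 × 0.7 + 0.6 × 0.4)]² / 0.30² = 41.97, so 42 evaluable per group.

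Then 42 / 0.8 = 52.5, so 53. The unpooled formula gives 40, and 40 / 0.8 = 50. The stated 52 lies between, so it is reproduced as an enrolled number. After drop-out, 52 × 0.8 = 41.6, about 42 per arm.

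**4. What a falls row could show**

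The documents give no fall rate, so 10 to 30 % over follow-up is an assumption. With the same rate p in both arms, the half-width of the 95 % CI for the difference is 1.96 √(2p(1 − p)/n).

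| Assumed p | Fallers per arm, n = 52 | Half-width, n = 52 | Fallers per arm, n = 42 | Half-width, n = 42 |
|---|---|---|---|---|
| 10 % | 5.2 | ±11.5 points | 4.2 | ±12.8 points |
| 20 % | 10.4 | ±15.4 points | 8.4 | ±17.1 points |
| 30 % | 15.6 | ±17.6 points | 12.6 | ±19.6 points |

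**The case against.** A reader might infer that falls will never be counted. The text does not support that. The *Adverse events* section opens with a broader intention to measure events possibly associated with either intervention, and its list is introduced as examples. A fall attributed to the exercises could be recorded, a fall followed by marked back or leg pain could be counted under a listed symptom, and a serious one could reach the ethics board. The safety monitoring protocol is not reproduced and may name falls. The absence of falls from Table 2 proves little, because that table has no adverse-event row at all. All of this stands. It makes capture possible but leaves it ad hoc, and the incidence promise is still confined to the listed events.

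A reader might also infer that the protocol regards falls as the likeliest harm of treatment, or that a planned between-group safety comparison is undermined. Neither is in the text. The high-risk statement concerns the population and the SPWT, which both arms take on the same schedule. The safety plan is incidence with 95 % CI, with no between-group comparison stated.

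Finally, one may say that intervention-related events and test safety are separate subjects, that restricting adverse events to the former is a legitimate choice, and that a full protocol may hold the detail. In part this is so. But the article does not defer the matter: it states a definition, a list and an analysis rule, and a fall during home exercise sits on the boundary that the rule leaves unclear.

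**Conclusion.** The point holds in a limited form. As stated, the definition, the list and the incidence rule leave falls and injuries out of the planned safety results, while the Discussion names both as risks. Some falls may still be recorded, but that would depend on who attributes them to what, and on roughly four times as many enquiries in Group 1 as in Group 2.

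The size of the loss cannot be fixed from the documents. Under the assumed 10 to 30 %, about 5 to 16 of 52 participants per arm would fall (4 to 13 of about 42 after drop-out) without a defined place in the safety tables. A falls row would be descriptive: at 20 % in each arm its precision is about ±15 points with 52 per arm and ±17 points with about 42, so only a large difference would stand out. The primary walking result is unaffected.

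**What to change.** Reconcile the *Adverse events* section with the Discussion:

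1. Add fall (any; with injury) to the listed adverse events, regardless of attributed cause.
2. Ask the same fall question, with the same recall period, at each scheduled follow-up in both arms. It can be asked by telephone when a participant cannot attend.
3. Log every fall during the SPWT. Show those at the baseline test separately, since it precedes randomisation.
4. Report descriptively, by arm, the number of participants with at least one fall and with at least one injurious fall, with 95 % CI. Use participants, not visits, as the denominator, and base the by-arm figures on the scheduled follow-up question rather than on the extra Group 1 treatment visits.

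Adverse events are already assessed at these follow-ups, so the cost is one question and a table row or two. The downside is a slightly longer follow-up interview. If the safety monitoring protocol already records falls, a sentence saying so, together with item 4, would be enough, provided that the recording is the same in both arms.

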## Background

Lumbar spinal stenosis (LSS) refers to an anatomical narrowing of the central and/or lateral spinal canals [1]. It is usually caused by age related degenerative changes in the spine including intervertebral disc thinning, facet joint thickening and in-folding of the ligamentum flavum [2]. These changes contribute to a decrease in cross-sectional area of the spinal canal that can lead to compression and diminished blood flow to the spinal nerves [3, 4]. The clinical syndrome caused by LSS is known as neurogenic claudication. This syndrome is characterized by bilateral or unilateral buttock, lower extremity pain, heaviness, numbness, tingling or weakness, precipitated by walking and standing and [5] relieved by sitting and bending forward [2, 6]. Neurogenic claudication due to LSS is a leading cause of pain, disability and loss of independence in people over the age of 65 [7]. Limited walking ability is the dominant functional impairment caused by LSS [2]. Those afflicted have greater walking limitations than individuals with knee or hip osteoarthritis [8] and greater functional limitations than those with congestive heart failure, chronic obstructive lung disease or systemic lupus erythematosus [7]. Inability to walk among individuals with LSS leads to a sedentary lifestyle and a progressive decline in health status [9, 10]. Furthermore, symptomatic LSS is also associated with increased levels of depression; anxiety and hopelessness that can further perpetuate disability [11–14].

The prevalence and economic burden of LSS is growing exponentially due to the aging population. In Japan where 25 % of the population is over the age of 65, about 12 million people suffer from symptomatic LSS [15]. A similar epidemic is expected in the US by the year 2030 when an estimated 73 million people will be over the age of 65 [16] of which 30 % are projected to have symptomatic LSS [17]. LSS is the most common reason for spine surgery in individuals over the age of 65 [18], however only very few patients receive surgery [19]. The vast majority of individuals with LSS receive non-surgical care. However, what constitutes effective non-surgical care is unknown [20–23].

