### Recruitment

Participating physicians and chiropractors will identify potential participants using an eligibility checklist (Table 1). Eligible potential participants will be given a pamphlet outlining information concerning the study and providing contact information for the trial coordinator. Interested and potentially eligible participants will be asked to contact the trial coordinator directly. Pamphlets will also be available in patient waiting rooms of participating hospital clinics and community clinics. Similar information will be advertised in local newspapers to enhance recruitment. The trial coordinator will provide details about the study and answer questions by phone. The coordinator will confirm eligibility including age, duration of symptoms and self-report walking ability. Walking ability will be assessed by the participants’ response to the question *“are you able to walk continuously for 30 min without the use of aids or without stopping to rest or stoop forward to alleviate your symptoms?*” Self-reported walking ability has been shown to be highly correlated (*r* = 0.80) to the self-paced walking test (SPWT) [31]. The SPWT is a validated objective measure of walking ability in LSS [31]. Only interested participants who respond “NO” and meet the other inclusion/exclusion criteria will be given an appointment for an intake assessment at the study site (Mount Sinai Hospital in Toronto Canada).

**Table 1 Tab1:** Inclusion and exclusion criteria

Inclusion criteria	
1. Age greater or equal to 50 years	
2. Clinical symptoms of back and/or radiating lower limb or buttock pain; fatigue or loss of sensation in the lower limbs aggravated by walking and/or standing and relieved by sitting.	
3. Intermittent or persistent pain without progressive neurological dysfunction	
4. Duration of symptoms and signs for more than 3 months	
5. Imaging confirmed spinal canal narrowing using MRI, CT scan, myelography or ultrasound	
6. Clinical signs and symptoms corresponding to segmental level of narrowing identified by imaging	
7. Patients with degenerative spondylolisthesis are included	
8. Not considered to be a surgical candidate (in the next 12 months) or patient unwilling to have surgery	
9. Able to perform mild-moderate exercise	
10. Able to walk without assistive devices for at least 20 m and less than 30 min continuously	
11. Able to give written informed consent and complete interviews and questionnaires in English.	
Exclusion criteria	

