##### Symptom severity

This will be measured using the symptom severity scale of ZCQ. The symptom scale consists of seven questions pertaining to overall severity of pain, pain frequency, back pain and, pain in the leg, numbness, weakness and balance disturbance. The scale has a high internal consistency with a Cronbach’s coefficient of 0.87, a test-retest reliability correlation coefficient of 0.92 and a responsiveness of 0.86 using the standardized mean [45, 46]. The MCID is estimated to be 0.5 [45].

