##### Co-interventions

We will measure co-interventions by asking participants to self-report the type and frequency of consultations with other health care providers and the type of interventions received beyond those provided in the trial. This would include physiotherapy, chiropractic, massage therapy, acupuncture, epidural injections and surgery. We will also ask participants if they have used medications and the frequency of use for their back and/or leg symptoms.

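### New or worsening leg weakness and progressive neurological dysfunction are not on the adverse-event list, so the incidence analysis, which is tied to that list, would not report them separately

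*Protocol article*

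**What the plan says.** The section on adverse events in the protocol article does three things in sequence. It sets a broad definition: "We will define adverse events as an unintended sign or symptom of the intervention". It gives examples: "These include: significant increase in back and/or lower extremity pain, numbness, tingling, tiredness or claudication and cauda equine syndrome". It then fixes the analysis: "We will compute the incidence (95 % CI) of each adverse event listed above", with the cumulative number of visits as denominator. Separately, any life-threatening or significantly disabling event is to be reported to the ethics board.

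Other sections bear on what the list leaves out:

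- The Background describes the syndrome as "lower extremity pain, heaviness, numbness, tingling or weakness, precipitated by walking and standing", and adds that nerve root compression, together with disuse, can reduce leg strength.
- Inclusion criterion 3 in Table 1 reads "Intermittent or persistent pain without progressive neurological dysfunction"; exclusion criterion 1 names progressive neurological dysfunction again.
- The ZCQ symptom scale has seven questions, the last of which cover "pain in the leg, numbness, weakness and balance disturbance". Table 2 schedules it at every follow-up.
- Surgery is collected among the co-interventions: "This would include physiotherapy, chiropractic, massage therapy, acupuncture, epidural injections and surgery".

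**The concern.** The definition is open and the analysis is closed. Whatever is recorded, only the events named in the list are assigned an incidence. Weakness is part of the protocol's own description of the syndrome, and neurological progression is a state that participants must not have at entry, yet neither becomes a counted category afterwards.

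The arms differ in a way that makes the comparison relevant. Group 1 receives manipulation and neural mobilization at up to 13 sessions (twelve plus one booster), and Group 2 receives no manual therapy. If the plan is followed as written, the published safety table could be silent on motor deterioration because it has no row for it. Readers could take that silence as evidence that none occurred.

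**Working it through.** No figure in the plan needs recomputing for this point; the check is a comparison of passages.

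**Step 1. The syndrome against the list.**

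| Symptom in the Background | On the adverse-event list? |
|---|---|
| Pain | Yes |
| Numbness | Yes |
| Tingling | Yes |
| Heaviness | Not by name; tiredness is the nearest entry |
| Weakness | No |

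The list adds claudication and cauda equina syndrome. Progressive neurological dysfunction, the term used in Table 1, does not appear.

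**Step 2. What the analysis sentence covers.** It covers incidence "of each adverse event listed above". An event that meets the definition but is not on the list can be recorded and still receive no incidence.

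**Step 3. Where a case of new weakness would go.**

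- Weakness brought on by walking: could be coded as increased claudication, since the Background describes claudication as including weakness. It would not be visible separately.
- Weakness as part of cauda equina syndrome: listed.
- Weakness with significant disability: reported to the ethics board, but this is case reporting and gives no incidence by arm.
- Fixed or progressive weakness short of cauda equina syndrome: no clear listed category.

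**Step 4. Whether another measure supplies the count.**

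- A physical examination is described at intake. Table 2 shows no neurological examination at follow-up.
- The Short Physical Performance Battery (SPPB) is repeated at every follow-up, but it measures function and balance. It also needs attendance, because only self-report measures are given by telephone.
- The ZCQ weakness item is asked at every follow-up, and by telephone if need be, but it enters a seven-item score. Assume an unweighted mean, as the article states for the physical performance scale. A worsening of *k* points on that item alone then moves the score by *k*/7: 1/7 = 0.14 and 2/7 = 0.29. To move it by the stated minimal clinically important difference of 0.5 would take 7 × 0.5 = 3.5 points on the single item. That difference is a benchmark for the scale and not a safety threshold. The arithmetic shows only that the scale score is a poor place to see a change in one item.
- Surgery is collected at each follow-up, but as a co-intervention.

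**The case against.** The strongest reply is that the list only illustrates. It opens with an inclusive phrase under a broad definition, so treatment-related weakness is an adverse event whether named or not. Exertional weakness has a listed home under claudication. Disabling cases go to the ethics board regardless of the list. The SPPB gives a repeated, assessor-administered view of leg function. The Discussion commits to comparing co-interventions between groups and mentions a safety monitoring protocol, tied to the single-session group, which is not shown. A journal article also condenses; the layout of safety tables often sits elsewhere.

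Most of this stands, and it limits the point. A reader might infer that the trial cannot record or count motor deterioration at all; the open definition rules that out. A reader might also read the entry criteria as guarding specifically against leg weakness. Table 1 speaks of progressive neurological dysfunction and does not say that; the link to weakness is an interpretation that the Background makes reasonable. Nor is it sound to work out an upper risk limit from zero cases among the 52 participants per group. The plan divides by visits and would report no zero for an event that is not listed.

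What the reply does not answer is the analysis sentence. The article does not leave the scope of the incidence analysis to another document; it states it and confines it to the list. Recording an event or notifying the ethics board does not produce an incidence. The planned comparison of co-interventions is there to help interpret the results and is not presented as a safety outcome.

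**Conclusion.** The point holds as a mismatch between an open definition and a closed analysis. Lower-limb weakness and progressive neurological dysfunction would receive no separate incidence, and the part with no clear listed category is a fixed or progressive motor deficit short of cauda equina syndrome.

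The size cannot be put in cases: the documents give no rate for such events, and any assumed one would be arbitrary. No primary or secondary efficacy result is affected. The conclusion rests on two assumptions: that the incidence sentence will be followed as written, and that neurological progression in this population can show as leg weakness, which the Background supports but Table 1 does not state. It is a worthwhile, low-cost improvement to the safety report and does not show that harm would go unrecorded.

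**What to change.** 1. Add *new or worsening lower-limb weakness / progressive neurological dysfunction* to the adverse-event list, or extend the incidence analysis to all recorded adverse events. Either one reconciles the definition with the analysis.
2. In the safety report, tabulate by arm: (a) participants whose ZCQ weakness item worsened from baseline at each follow-up, and (b) participants who had lumbar surgery during the 12 months, taken from the co-intervention data.
3. Count these per participant. Adverse events are asked about after each of up to 13 treatment visits plus four follow-ups in Group 1 (17 occasions), but only at the four follow-ups in Group 2, so a visit-based rate would not be a like-for-like comparison.

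The cost is one list entry and one safety table; the tabulations in item 2 need no new measurement. The drawback is that the ZCQ item will pick up some natural fluctuation, so it should be read as a comparison between arms and not as a count of confirmed motor deficits. Nothing here changes treatment or clinical management.

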**Discussion:**

Symptoms and functional limitations in LSS are variable and influenced by changes in spinal alignment. Physical and psychological factors result in chronic disability for patients with LSS. The Boot Camp Program is a 6-week self-management training program aimed at the multi-faceted aspects of LSS and trains individuals to use self-management strategies. The goal is to provide life-long self-management strategies that maximize walking and overall functional abilities and quality of life.

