##### Functional disability

Functional disability will be measured by the Oswestry Disability Index (ODI) [47]. The ODI is a reliable and validated measure of back-related disability where 0 represents no disability and 100 represent the worse possible disability. We will also record separately the score of the walking section (ODI walk) of the ODI. The ODI walk score has been shown to be highly correlated to objective walking distance (*r* = 0.83). The MCID for the ODI is 8–12 percentage points [48].

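### Adverse-event incidences will not be comparable between arms: symptom increases with no stated reference point are counted after every session in Group 1, only at follow-ups in Group 2, and divided by visits

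*Protocol article*

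**What the plan says.** In the protocol article, Adverse events section:

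- Definition: "We will define adverse events as an unintended sign or symptom of the intervention". Attribution to treatment is therefore part of the definition.
- Listed events: "significant increase in back and/or lower extremity pain, numbness, tingling, tiredness or claudication", plus cauda equina syndrome. No comparison time, size or duration is attached to the increase.
- Timing: "This will take place following each visit for participants enrolled in Group 1"; in addition, both groups are asked at each follow-up visit.
- Analysis: an incidence with 95 % CI for each listed event, with cumulative visits as the denominator.

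Group 1 has twelve sessions and one booster (section on Group 1). Group 2 has one instructional session (section on Group 2). Data collection and follow-up, and Table 2, place follow-ups at 6 weeks and 3, 6 and 12 months for everyone. The abstract gives 8 weeks for the first; that does not change the count.

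The Background describes pain, numbness and tingling as features of neurogenic claudication itself, and the abstract says "Symptoms and functional limitations in LSS are variable and influenced by changes in spinal alignment".

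The back and leg pain NRS, the ZCQ and the ODI are collected at baseline and at all four follow-ups in both arms. For the ZCQ symptom scale, "The MCID is estimated to be 0.5". For the other, "The MCID for the ODI is 8–12 percentage points". No MCID is given for the NRS. The Adverse events section uses none of these scales.

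**The concern.** Most listed events are increases in symptoms that belong to the disease and vary without treatment. A count of them depends on how often one asks and over what interval the participant looks back, and the arms differ on both. Group 1 is asked twice a week for six weeks. Group 2 is first asked at 6 weeks, so a short reaction to the home exercises is recorded only if it is recalled. One label can thus cover brief reactions in one arm and mainly remembered or persisting worsening in the other, and dividing by visits does not restore comparability.

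At stake is whether a reader can compare harm between a programme with manual therapy and a single instructional session. The figures could mislead in either direction.

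**Working it through.** The plan states no adverse-event rate, threshold or precision, so there is no figure of its own to reproduce here. The 52 per group belongs to the primary outcome and is not used.

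**1. Occasions on which events are sought (full attendance)**

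- Group 1: 12 sessions + 1 booster + 4 follow-ups = 17.
- Group 2: 4 follow-ups.
- Ratio: 17/4 = 4.25.

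**2. Effect of the visit denominator**

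Let *f* be the chance of an event at a follow-up, assumed equal in both arms, and *s* the chance of an event at a Group 1 session. Then:

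- Group 1 incidence per visit = (13*s* + 4*f*)/17
- Group 2 incidence per visit = 4*f*/4 = *f*
- Ratio, Group 1 to Group 2 = (13·*s*/*f* + 4)/17

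The documents do not give *s*/*f*, so a range is assumed:

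| *s*/*f* (assumed) | Ratio |
|---|---|
| 0 | 4/17 = 0.24 |
| 1 | 17/17 = 1.00 |
| 2 | 30/17 = 1.76 |

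The article does not say which visits count. If Group 2's single session also enters its denominator, Group 2's incidence is 4*f*/5 and each ratio is multiplied by 5/4: 0.29, 1.25 and 2.21. On either count, identical worsening at follow-up gives equal incidences only for one particular value of *s*/*f*.

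**3. Sensitivity to the unstated threshold (illustration only)**

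Assume no true change and a normal change from baseline in the NRS with SD between 1.5 and 3 points. The SD is an assumption; the documents give none. The share flagged at one assessment for a rise of at least *t* points, with a half-point allowance for the integer scale, is 1 − Φ((*t* − 0.5)/SD).

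| *t* | SD 1.5 | SD 2 | SD 3 |
|---|---|---|---|
| 1 | 37 % | 40 % | 43 % |
| 2 | 16 % | 23 % | 31 % |
| 3 | 5 % | 11 % | 20 % |

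Moving *t* from 3 to 1 multiplies the count by about 2 (SD 3) to 8 (SD 1.5). This shows that the count is elastic. It is not an estimate of a difference between arms, and the NRS is not scheduled at treatment sessions.

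**4. What the collected scales can anchor**

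- Pain: NRS and ZCQ symptom items.
- Numbness: a ZCQ symptom item.
- Tingling and tiredness: no scale is described as covering them.
- Disability: the ODI, which is not a listed event but has a stated MCID.

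All are available at baseline and the four common follow-ups, and by telephone if a participant cannot attend. None is available after Group 1 sessions.

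**The case against.** Thresholds and grading for adverse events are often left to a full protocol or safety plan, and the Discussion mentions a safety monitoring protocol that is not shown. That stands: an unprinted threshold alone would not be a finding in a journal article. But the article itself fixes the event list, the unequal timing and the visit denominator, and those together produce the problem.

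Three stronger readings are tempting and not supported:

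- A reader might infer that Group 1 events are judged against the previous session, so that slow worsening escapes. No text sets a visit-to-visit comparison or rules out baseline, and gradual worsening could still be recorded at 6 weeks.
- A reader might infer that the trial cannot say whether the programme makes patients worse. The Statistical analysis section plans mean differences with intervals at each follow-up for continuous secondary outcomes, which include the NRS, ZCQ and ODI. Net average worsening would show.
- A reader might infer that all event reporting is exposed to unblinded judgement. Practitioners and participants are unblinded, but a blinded assessor conducts the follow-ups. Participants' own reports remain unblinded, and that applies equally to the scales proposed below.

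The article also announces no formal between-arm safety test. Even so, incidences reported for each group in a two-arm trial will be read side by side.

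**Conclusion.** The point holds in a limited form. As printed, the adverse-event incidences are not comparable between arms and mix short-lived reactions with sustained worsening. The firm part is the 17-to-4 imbalance in ascertainment, the missing reference point and the per-visit denominator. The ratios from 0.24 to 1.76 assume full attendance, equal worsening at follow-up and a chosen range of *s*/*f*; they show that the bias can run either way. What is missing is a comparable event incidence and a view of any subgroup that deteriorates behind a favourable mean, not all evidence of harm. This is a worthwhile, inexpensive improvement to the safety analysis and does not affect the primary outcome.

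**What to change.** 1. Keep the adverse-event definition, including attribution and the tingling and tiredness events. State the reference time for an increase.
2. Restrict the between-arm safety summary to the common 6-week, 3-, 6- and 12-month follow-ups, with participants rather than visits as the denominator.
3. Report Group 1 session-by-session events as a separate descriptive listing.
4. Add a table of the proportion in each arm who worsen from baseline by at least 0.5 on the ZCQ symptom scale, and by at least 12 points on the ODI (upper end of the stated range), at each follow-up, with risk difference and 95 % CI. An NRS threshold may be added if fixed in advance, since the article gives none.

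The cost is some wording and one table, with no new data, visits or staff. The drawbacks are that short-lived reactions between follow-ups appear only descriptively, that the scales are still self-reported by unblinded participants, and that applying the stated MCIDs to worsening is a choice the plan should declare.
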